## Objectives

Our primary goal is to assess the efficacy of an 8-week group intervention combining hypnosis and self-care to improve fatigue in all types of cancer patients, after treatments. The secondary goals are to assess the efficacy of this intervention to improve other patients’ well-being-related variables (emotional distress (anxiety and depression), sleep, fear of cancer recurrence, psychological adjustment to the disease, emotional regulation skills, cognitive functioning, and physical activity). As the intervention will address various fields such as communication with relatives, we will also assess its impact on the couple’s dynamic, and on partner’s distress. Finally, the link between the decrease in patients’ distress and a possible attentional bias will be assessed in order to better understand the emotional regulatory mechanisms in cancer patients.

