#### Tasks

Three tasks are suggested to the participants:*Two relaxation exercises:* Anxiety regulation is measured during two relaxation exercises. Before each exercise, anxiety is triggered by the completion of the MAC (before exercise 1) and the ICQ (before exercise 2) questionnaires. During the first exercise, participants have to use their own strategies to relax by themselves for about 13 mins, and during the second, they are guided by an audio recording for approximately the same time. Heart rate (beats per minute) is measured during the exercises by the Lifecard CF holter monitor as an indicator of anxiety regulation [85]. Heart rate variability has been shown to be correlated with emotion regulation [86] and influenced by emotional distress (depression and anxiety) [87, 88].*An attentional task:* A computerized task is used to assess the attentional bias toward threat. This computerized task, designed by the Université Libre de Bruxelles (ULB, Belgium), aims to evaluate the intensity of the attentional bias toward emotional information. Several pairs of words (each word being positive, negative, or neutral; and related or not related to cancer) are presented to the participants, followed by a point, located at the same place as one of the two words. The participants have to click on the up or down button of the keyboard depending of the location of the point. An increased response time for points following cancer-related words could suggest the presence of an attentional bias towards threat. Response time and accuracy will be measured in order to calculate different attentional bias indexes [18], which will evaluate the severity of the bias before and after the intervention.

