### Statistical analyses

Baseline (T1) demographic, medical, and psychological data will be compared between groups to test for initial groups equivalency using inferential statistics, including analyses of variance (ANOVA) and chi-square tests. Group-by time changes, and pre- and post-assessment comparison of each variable within each group will be assessed using repeated measures MANOVA, on the participant who completed all the needed assessments times. The link between a decrease in distress and attentional bias will be assessed by correlations. Correlations will also be used to assess the links between the data from the patients and their partners, and we will measure the evolution of the partners using repeated measures MANOVA. All tests will be two-tailed, and the alpha will be set at 0.05. Statistical analyses will be performed after T3 and after T4.

All participants will be informed by e-mail about the final results of the study. Scientific publications will also be planned.

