## Discussion

Few studies in oncology focus on CRF in cancer patients and interventions investigated in such studies are often traditional ones [37, 38]. Hypnosis-based interventions are starting to be evaluated as a way to improve quality of life as well [36, 40, 42]. However, long-term data about the effects of such interventions are missing, most studies included only breast cancer patients, and very few included partners in their assessments. Finally, very few studies have investigated the explanatory mechanisms of emotion regulation in cancer patients.

Thereby, our study would make a great contribution as it focuses on CRF, sleep, and emotional distress [6, 7, 34], and provide a long-term assessment of intervention effects. The randomised controlled design is also a strength of our study. Plus, it includes all types of cancer (except for metastatic ones) and all type of treatment, and evaluates the effects of the intervention on patients’ partners and on couple functioning. Finally, our study investigates the link between the attentional bias toward threat and emotion regulation, contributing to better understand the mechanisms of emotion regulation in cancer patients.

We made several hypotheses on the impact of the intervention: 1) fatigue and emotional distress will decrease in response to the intervention, and sleep and emotional regulation will improve; 2) dyadic coping and communication in the couple will improve, and partner’s distress will decrease; and 3) there will be a positive association between the decrease of patients’ distress and the decrease in the attentional bias.

These assumptions follow from the three major components of hypnosis that could influence cognition and emotional regulation: absorption, which is the involvement in a perceptual, imaginative or ideational experience; dissociation, which is the mental separation of different components of experience that would usually be processed as a whole; and suggestibility, which is the responsiveness to social clues, enhancing the propensity to comply with hypnotic instructions and suspending critical judgment [93]. Those hypnotic suggestions also seem to facilitate mind-body connection and lead to physical, emotional and behavioral changes [94].

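### The correlation planned for hypothesis 3 specifies no arm adjustment; if computed over both arms while only one has been treated, a shared treatment effect can by itself make it positive

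*Protocol article*

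**What the plan says.** Hypothesis 3, in the Discussion, is that "there will be a positive association between the decrease of patients’ distress and the decrease in the attentional bias". The Objectives give its purpose: "the link between the decrease in patients’ distress and a possible attentional bias will be assessed in order to better understand the emotional regulatory mechanisms". The only analysis named for it, under Statistical analyses, is that "The link between a decrease in distress and attentional bias will be assessed by correlations". That sentence does not say which patients enter, over which interval, or whether arm is taken into account. In the same paragraph the repeated measures MANOVA is given an arm structure: group-by-time changes, and pre-post comparisons inside each group.

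Three other statements bear on the point:
- Hypothesis 1 expects that "fatigue and emotional distress will decrease in response to the intervention".
- Under Tasks, the attentional bias indexes are ones "which will evaluate the severity of the bias before and after the intervention".
- For couples, "Correlations will also be used to assess the links between the data from the patients and their partners", again with no mention of arm, and without saying whether levels or changes are correlated.

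The general rule is that "All tests will be two-tailed, and the alpha will be set at 0.05".

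**The concern.** In a randomised comparison with a waiting list, arm can be a common cause of two change scores. If treated patients improve on both variables and waiting-list patients improve on neither, the two arms form two clouds of points displaced along the diagonal. A correlation over all the points is then positive, although within each cloud a patient whose distress fell more shows no greater fall in bias.

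The authors intend to read the correlation as information about how emotion regulation works. A correlation that comes only from the difference in arm means says that the intervention affected both outcomes, which the MANOVA is already there to show. It says nothing about whether the two changes go together from patient to patient. The error also favours the hypothesis, because almost all the excess rejections are in the predicted direction.

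**Working it through.** **Inputs from the protocol article.** 44 patients per arm, 88 in total; two-sided alpha 0.05 (Recruitment; Statistical analyses).

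**Check of the stated sample size.** For an independent-samples t-test with d = 0.7, alpha 0.05 and power 90%, the noncentral t calculation gives 43.87, hence 44 per arm, with power 90.1% at 44. The stated figure reproduces. That 0.7 is a general planning value and is not assigned to distress or to attentional bias.

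**Assumptions.** Let d1 and d2 be the arm differences in the decrease of distress and of bias, in within-arm standard deviations. The article gives neither, so a range is shown. Both changes are taken as normal, with zero correlation within each arm.

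**Induced correlation.** With equal arms, the difference in means adds d1·d2/4 to the covariance, and d1²/4 and d2²/4 to the two variances. So

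r = (d1·d2/4) / √[(1 + d1²/4)(1 + d2²/4)].

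At 0.7 on both: 0.7 × 0.7 / 4 = 0.1225; each variance is 1 + 0.1225 = 1.1225; r = 0.1225 / 1.1225 = 0.109.

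**Rejection rate.** At N = 88 the two-sided 5% critical value of r is 0.21. As a rough check at 0.7 on both, the expected t is 0.109 × √[86 / (1 − 0.109²)] ≈ 1.02, and the chance that a standard normal exceeds 1.96 − 1.02 = 0.94 is about 17%. Simulation with 400,000 trials per row gives:

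| d1 (distress) | d2 (bias) | induced r | unadjusted test rejects | arm-adjusted test rejects |
|---|---|---|---|---|
| 0.7 | 0 | 0.00 | 5.0% | 5.0% |
| 0.3 | 0.3 | 0.02 | 5.5% | 5.0% |
| 0.7 | 0.3 | 0.05 | 7.4% | 5.0% |
| 0.5 | 0.5 | 0.06 | 8.5% | 5.0% |
| 0.7 | 0.5 | 0.08 | 11.5% | 5.0% |
| 0.7 | 0.7 | 0.11 | 17.4% | 5.0% |
| 1.0 | 0.7 | 0.15 | 28.2% | 5.1% |
| 1.0 | 1.0 | 0.20 | 47.6% | 5.0% |

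At 0.7 on both, 17.3 of the 17.4 percentage points are significant positive correlations, against a nominal 2.5 in that direction.

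**Interval.** The design gives the waiting-list arm the intervention at the latest 4 months later. The first intervention group started in April 2017 and its waiting-list group in July 2017, so an eight-week course ends before the second begins. T1-T2 is therefore the natural interval with one arm treated. The exact schedule is in Figure 1, which is not shown. Over an interval in which both arms have been treated, the arm difference shrinks, and the induced correlation with it.

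**The case against.** The strongest reply is that the article nowhere says the arms are pooled. A reader might infer that it does, because the correlation sentence carries no arm structure while the MANOVA sentence does. That is an inference. The bias indexes are described as before-and-after measures, and hypothesis 3 is listed among the effects of the intervention, so an analysis of treated patients only, or within each arm, fits the text too and would not have this problem. The article is also condensed, and an analysis plan that is not shown may settle the matter. This stands: the point is conditional and is not a demonstrated error.

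Second, the effect on attentional bias is uncertain. Hypothesis 1 does not name it, the Objectives call the bias only a possible one, and no size is given. A reader might take 17% as the protocol's own error rate because 0.7 is its planning value. The article does not support that, and with no effect on bias there is no inflation at all. This stands too.

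Third, a reader might extend the fault to every patient-partner correlation. The article does not say those use change scores. At baseline no treatment effect yet exists to induce a correlation, so baseline correlations are unaffected.

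Fourth, it is tempting to say that the analysis sentence uses the level of bias while the hypothesis uses its decrease. The sentence can equally be read as a decrease in both, and the Discussion is explicit on "a positive association between the decrease of patients’ distress and the decrease in the attentional bias". The wording is loose, but it is not a contradiction.

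What survives is that the only named test of a stated hypothesis, applied to all randomised patients, has an error rate that depends on how well the intervention works. A version that avoids this is available from the same data.

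**Conclusion.** The point holds in conditional form. Unadjusted correlation over both arms does not test whether the two decreases are associated apart from treatment. Three conditions are needed for harm: both arms enter the correlation, the interval is one in which only one arm has been treated, and the intervention moves both variables. Under assumed effects the false-positive rate with 44 per arm then runs from about 5% to about 48%, and is about 17% at 0.7 on both. The relevant null is no association within arms, since these are correlations between patients of their change scores. The analysis is secondary, and neither the primary fatigue comparison nor the sample size is affected. The change is worth making because the arm-adjusted test holds 5% whatever the arm effects are.

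**What to change.** Replace the correlation sentence with one that names the variables, the interval and the adjustment: hypothesis 3 is tested by the partial correlation, adjusted for arm, between the T1-T2 decrease in HADS and the T1-T2 decrease in the attentional bias index (or the equivalent regression with arm as covariate). State that the bias variable is its decrease, as the hypothesis has it.

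For patients and partners, apply the same arm adjustment where post-intervention or change scores are correlated. Baseline correlations can stay as they are.

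The cost is one reworded sentence and one degree of freedom (85 instead of 86 at N = 88, which moves the critical r from 0.210 to 0.211). No new data are needed and the sample size stays at 88.

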### Eligibility

Inclusion criteria include several parameters:age 18 years or older;fluent in French;no history of psychiatric disorders, such as dementia, psychosis or delirium, which does not allow participation in a group intervention or completion of the evaluations;diagnosis of non-metastatic cancer (all tumour localisations accepted); we did not include metastatic patients in order to minimize baseline differences in the sample, as the changing nature and complexity of metastatic cancers could make it difficult to compare the results with non-metastatic cases [60];all active treatments completed for less than a year (surgery, chemotherapy, and/or radiotherapy), in order to form a group of participants who were recently involved in diagnosis and treatments and so increase the likelihood that the difficulties they are dealing with will be more similar;no relapse at the time of inclusion;difficulties as established by responses of at least 4 out of 10 on 1 of the 6 chosen items of the Edmonton Symptom Evaluation Scale [61]; these include physical fatigue, moral fatigue (we decided to split the original item “fatigue (lack of energy)” into two different items, in order to investigate both physical and psychological sides of fatigue), depression, anxiety, fear of recurrence, or ruminations. This cut-off score was chosen to avoid floor effects [59].

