#### Questionnaires

##### For patients

All questionnaires are detailed in Additional file 1: Appendix 1.

**General information:** Sociodemographic and medical data such as gender, age, language, professional activity, family members, personal history of cancer and treatment are collected. Some questions are also asked about life habits (physical activity, medication, alcohol and drug use, for example), and important life events.

**Physical and psychological functioning** is assessed through the use of several questionnaires: Visual Analogue Scales (VAS), the Edmonton Symptom Assessment Scale (ESAS) [61], the Hospital Anxiety and Depression Scale (HADS) [69], the Penn State Worry Questionnaire (PSQW) [70], the Fear of Cancer Recurrence Inventory (FCRI) [71], the Mental Adjustment to Cancer Scale (MAC) [72], the White Bear Suppression Inventory (WBSI) [73], the Multidimensional Fatigue Inventory (MFI-20) [74], the Cognitive Emotion Regulation Questionnaire (CERQ) [75], the Impact of Cancer Questionnaire (ICQ) [76], the Insomnia Severity Index (ISI) [77], the Five Facets Mindfulness Questionnaire (FFMQ) [78], the Post-traumatic Growth Inventory (PTGI) [79] and the Rosenberg’s self-esteem scale [80].

**Cognitive functioning** is assessed with the Functional Assessment of Cancer Therapy – Cognitive Function (FACT-Cog v.3) [81] and the Metacognition Questionnaire (MCQ-30) [82].

**Conjugal functioning** is assessed using two questionnaires: the Couples’ Illness Communication Scale (CICS) [83] and the Dyadic Coping Inventory (DCI) [84].

**Relaxation strategies** is investigated using two questionnaires about relaxation strategies used during the first exercise and about relaxation habits. These were created for the study.

Finally, the **questionnaire about the intervention** is focused on expected and perceived benefits from the intervention both for oneself and the partner (open questions).

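### The primary fatigue claim is not tied to one score, time point and contrast, while each variable is tested between and within arms at 0.05

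*Protocol article*

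**What the plan says.** The Objectives section of the protocol article states: "Our primary goal is to assess the efficacy of an 8-week group intervention combining hypnosis and self-care to improve fatigue". It ranks the other patient outcomes as secondary.

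The Statistical analyses section then sets one scheme for everything: "Group-by time changes, and pre- and post-assessment comparison of each variable within each group will be assessed using repeated measures MANOVA". The error level is uniform: "All tests will be two-tailed, and the alpha will be set at 0.05". On timing it adds: "Statistical analyses will be performed after T3 and after T4". It gives no order of testing and names no deciding variable.

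Fatigue can be read from more than one place:
- The MFI-20 and the complete ESAS are both given at T1 to T4 (Table 1).
- For the screening version of the ESAS, the Eligibility section says of the fatigue item that "we decided to split the original item" into a physical and a moral part.
- The smartphone application records energy level (Ecological momentary assessments).

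The Recruitment section sizes the trial with one independent-samples t-test (alpha 0.05, power 90%, standardized effect 0.7), giving 44 per group. The outcome behind that test is not named.

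**The concern.** A 5% error rate and 90% power describe a trial in which one test decides. As written, a fatigue claim could rest on any of several scores, at more than one time point, and from a between-arm or a within-arm comparison.

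The within-arm comparison is the weaker basis. The Design section justifies the waiting list as a control for natural recovery and spontaneous change in symptoms. The test described as "pre- and post-assessment comparison of each variable within each group" sets that control aside. Patients enter within a year of completing treatment, so some change without the intervention is foreseeable. A significant pre-post fall in the treated arm would look like support for the first hypothesis in the Discussion, which is worded as a decrease in fatigue and distress, whether or not the intervention did anything.

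**Working it through.** **1. The plan's own figure.** Inputs from Recruitment: d = 0.7, two-sided alpha 0.05, power 90%.
- Normal approximation: n per arm = 2 × (1.960 + 1.282)² / 0.7² = 42.9, so 43.
- Noncentral t: 43.87, so 44 per arm, with power 90.1% at 44.

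The stated 44 per group is reproduced. It is right for one test.

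**2. Several fatigue scores, between arms only.** For k independent tests at 0.05, the chance of at least one false positive is 1 − 0.95^k. Correlated tests were simulated with equal correlation between all pairs (100,000 runs).

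The count is an assumption: the MFI-20 as one score, one or two ESAS fatigue items, and possibly smartphone energy.

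| k | Independent | Correlation 0.5 | Correlation 0.7 |
|---|---|---|---|
| 3 | 1 − 0.95³ = 14.3% | 12.6% | 11.1% |
| 4 | 1 − 0.95⁴ = 18.5% | 15.7% | 13.1% |

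The count can be moved in both directions. With only the MFI-20 and one ESAS item, the independent figure is 1 − 0.95² = 9.75%. If subscales of the MFI-20 were tested separately and the total reached seven scores (the document does not give the number of subscales), it would be 30% if independent and 18% at correlation 0.7.

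**3. Within-arm test with no treatment effect.** Assume a T1-T2 correlation of 0.5. The SD of the change is then √(2 × (1 − 0.5)) = 1 SD. For a natural change of δ SD in 44 patients, the paired t-test has noncentrality δ × √44.

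| Assumed natural change | Noncentrality | Chance of p < 0.05 in one arm |
|---|---|---|
| 0.2 SD | 1.33 | 25% |
| 0.3 SD | 1.99 | 49% |
| 0.4 SD | 2.65 | 74% |

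The document gives no figure for natural change, so these values show a range and are not estimates.

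**4. Keeping several co-primary scores instead.** With Bonferroni and d = 0.7:
- Three scores (alpha 0.05/3 = 0.0167): power at 44 per arm falls to 79.8%, and 57 per arm are needed for 90%.
- Four scores (alpha 0.0125): 76.6%, and 60 per arm.

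One named primary test keeps 90.1% at 44 per arm.

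**The case against.** The best defence is that the article already says where efficacy is judged. The Methods part of the Abstract compares the experimental group with the control group to test efficacy. Recruitment powers the trial for a difference between groups in how the data evolve, and Design gives the waiting list the job of controlling natural recovery. The within-group comparisons are listed but never called efficacy evidence. This stands: a reader might infer that the plan makes within-arm change its efficacy rule, and the documents do not say so. The fault is that the analysis section puts the two kinds of test side by side at the same level without ranking them.

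Several narrower points also stand:
- The MFI-20 is the only dedicated fatigue instrument. The ESAS split is described for screening only, and the energy rating sits under emotional regulation. The count of three to four is therefore an assumption.
- Entry needs at least 4 out of 10 on just one of six items, several of them not about fatigue. Regression to the mean in fatigue may be small.
- T4 is a one-year follow-up with a shorter battery, after each patient has had the intervention. It is not a second look at the same test.
- An omnibus MANOVA could give some protection. However, the text speaks of each variable and makes no later test depend on an earlier one.

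It can also be said that a condensed article leaves multiplicity to the full protocol or SAP, which are not shown. That would answer a silence. Here the article states a rule, and a SAP that followed it would inherit the problem.

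**Conclusion.** The concern holds in a limited form. The primary goal is not tied to one score, time point and contrast, although the sample size presumes a single between-group test. For the fatigue claim between arms, the false-positive chance is about 14 to 19% if three to four measures are independent and 11 to 13% at correlation 0.7. That is two to four times the nominal level, but it does not make a false claim likely. Within-arm tests are uninformative about efficacy. The 25%, 49% and 74% depend on the assumed natural change and on the assumed correlation of 0.5.

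A reader might go further and count the 18 patient questionnaires (14 + 2 + 2 in the Questionnaires section): 1 − 0.95^18 = 60% for at least one false positive. That figure needs 18 independent scales, which is implausible for overlapping distress, worry and fatigue measures; it falls to 28% at correlation 0.7. It also concerns mostly outcomes that the Objectives rank as secondary, and nothing says that a significant secondary outcome counts as trial success. It is not the error rate of the headline conclusion. The sample size calculation itself is not in error.

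**What to change.** Before any outcome analysis, amend the Statistical analyses section to match the Abstract and Recruitment:

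1. Name one MFI-20 score, one time point before the waiting-list arm is treated, and the between-arm contrast as the sole primary test at two-sided 0.05.
2. Report within-arm pre-post changes as descriptive summaries only.
3. Label all other outcomes, including the remaining fatigue measures, as secondary or exploratory. Give confidence intervals and state that multiplicity is not controlled. A Holm procedure on a short list of secondaries is optional.

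This is a change of wording. It needs no extra patients, and 44 analysed per arm keep 90.1% power at d = 0.7. The price is that fewer results can be called significant.
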